***Relative to the intervention***		
(1) Satisfaction of primary caregivers with the intervention	• The scores on the Treatment Acceptability and Preference Questionnaire (TAP) [42], completed on day 4 after delirium onset will help assess caregivers appreciation of the intervention. This questionnaire contains 5 items on which appreciation is scored using Likert scales, the higher the scores the more appreciation. The reported α is ≥0.80.	
	**Intervention group only**	
(2) Availability necessary to provide the intervention		• Total amount of time allocated to each contacts provided through the intervention
		• Duration of the presence of the intervention
		• Duration of the presence of the primary caregivers for the intervention
		• Moments of the day which took place at the bedside visits on T1, T2, and T3
		**Intervention group only**
(3) Material resources		• Costs relative to printed documents and electrodes used to measure cerebral oximetry
(4) Fidelity to the components and structure of the intervention	• Number of encounters received/planned	• Modalities of intervention planned versus received
	• Reasons for encounters not received	
	I**ntervention group only**	**Intervention group only**
(5) Selection and use of delirium management behaviors	• Number of suggested behaviors in comparison to adopted behaviors by the primary caregivers	• Clinical condition of the patient at each visit
	**Intervention group only**	• Number and type of behavior adopted by the intervention provider at each visit on T1, T2, and T3
		• Number and type of behavior adopted by the primary caregiver at each visit on T1, T2, and T3
		**Intervention group only**

The primary objective of this pilot study is to examine the acceptability and feasibility of the study design, the experimental nursing intervention and a novel measure.

To evaluate the acceptability and feasibility of the study design, the following variables will be measured throughout the study: i) caregiver and patient recruitment; ii) randomization; iii) participant retention; iv) data collection; and v) between-group contamination. These were selected based on randomized pilot study evaluation criteria developed by Sidani and Braden [43], as well as other evaluation criteria. The primary indicator that will help assess the acceptability of the study design relates to the variable relative to caregiver and patient recruitment. This primary indicator is to obtain consent from at least 75% of the caregivers approached to participate in the study.

The acceptability and feasibility of the nursing intervention will be evaluated using measures inspired by the work of Sidani and Braden [43] including: i) satisfaction of primary caregivers with the intervention; ii) availability to provide the intervention; iii) material resources; iv) fidelity to the content and structure of the intervention; and v) selection and use of delirium management behaviors. Description of the nursing intervention will be done by using a log of visits by the caregivers and other family members and of the behaviors they adopted, with any comments describing the patient’s reaction. All nurse-caregiver encounters will be described using a pre-coded possible behaviors list with additional space for incoming new behaviors.

Evidence suggests that low oximetry levels are linked with a greater risk of delirium, [44] and while this technology could potentially improve delirium detection and monitoring as well as guide decisions about intervention, it must first be piloted before being introduced in a larger scale study. Oximetry values will be obtained for six different sites represented in Figure 1: low right frontal cerebral (1), high right frontal cerebral (2), low left frontal cerebral (3), high left frontal cerebral (4), one arm (5a or 5b), and one leg (6a or 6b). Electrodes will be placed on the higher and lower frontal cerebral areas to cover a larger zone. To obtain the _r_SO_2_ value for each of these six sites, the electrode is left in place for more than 20 seconds for stability of signal, after which the number appearing on the device is recorded. From these six _r_SO_2_ values, two mean scores are calculated: the total cerebral score being the mean score of all four cerebral sites, and the total peripheral score being the mean score of the two peripheral sites. Lower cerebral values and normal peripheral ones are indicative of poorer cerebral oxygenation not due to peripheral hypoperfusion. Given the novelty of cerebral _r_SO_2_ obtained using NIRS, we will describe the validity of this approach by contrasting the scores with three standard tools for the detection and assessment of delirium: the ICDSC, the Delirium Index (DI), and the Confusion Assessment Method (CAM-ICU). These tools will be used at Days 1, 2, and 3 following the onset of delirium.

**Figure 1 Fig1:**
[figure not shown]
**Oximetry measures sites.** In this figure are represented the six different measuring sites from which oximetry values were collected. Lower right frontal cerebral (1), upper right frontal cerebral (2), lower left frontal cerebral (3), upper left frontal cerebral (4), and the possible areas for oximetry measures taken from one arm (5a or 5b) and one leg (6a or 6b).

The secondary objective to examine the preliminary effect of the intervention on patient and caregiver outcomes will be measured using different research tools, including questionnaires described in Table 1.

### Sample size

Patients with delirium at either of these post-surgical units will be randomized along with their caregivers to either usual care or experimental group (Table 1). A convenience sample of 30 patient-caregiver dyads will be recruited based on the specific published literature on pilot studies [45–48]. Because of the high involvement needed from caregivers in this intervention, the indicator chosen to determine the feasibility of the study was set as obtaining consent from a proportion of 75% of the caregivers approached to participate in the study. With such a proportion, 30 dyads is a sample large enough to estimate the proportion of caregivers that consent with a precision of ± 15.5% using a 95% confidence interval. In addition, the chosen sample size will enable us to highlight any trend or possible differences in patient and caregiver outcomes between the two study groups.

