**Relative to the study design**		
(1) Caregiver and patient recruitment	• Primary indicator: obtaining consent from at least 75% of the caregivers approached to participate in the study	• Recruitment time
	• Percentage of eligible people who were included in the study	• Effectiveness of recruitment strategies
	• Caregiver reasons for refusal to participate in the study	• Number of potential participants
	• Difficulties in obtaining patient consent	
(2) Randomization	• Reasons for patient refusal to participate after the delirium episode	• Number of non-eligible participants randomized
(3) Participant retention	• Reasons for withdrawal from the study	
(4) Data collection	• Rate of completion of questionnaires	• Percentage of outcome measures collected
	• Reasons for non-completion of questionnaires	• Time required for completion of outcome measure tools
		• Respect of the data collection plan
		• Validity of cerebral oximetry as an indicator of delirium
(5) Between-group contamination	• Rate of participants in the control group exposed to the intervention (overlapping time for the intervention and usual care, e.g., because of prolonged hospital stay)	
		• Attendance rate of caregivers at the bedside
		• Moments of the day for which caregivers were present
		• Number of family members, other than the caregiver, who visited the patient
		• Relationships between visitors and the patient
		• Total time spent at the bedside by the caregiver
		• Total time spent at the bedside by other visitors

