### Recruitment

#### Original protocol

Recruitment for this study poses several challenges because study participants include postoperative patients with delirium which makes them temporarily unable to give informed consent. In the original protocol, we planned a preoperative screening to include only patients with high risk of delirium. This was defined as the presence of at least three of the following risk factors: age ≥ 65 years, history of delirium, active smoker, consumption of at least three daily alcoholic beverages, or sensory impairment (sight, hearing). Postoperative delirium was defined as a score of ≥4 on the ICDSC [19] confirmed by a medical diagnosis of delirium recorded in the hospital chart. Since it is impossible to predict whether and when delirium will occur, two recruitment steps were planned.

Step 1 – All patients admitted to the pre-surgical unit at the study hospital will be assessed for study eligibility before their surgery by the nurse-mentor. The aim and requirement of the study protocol will be presented to eligible patients. Patients who agree will give the name of a family caregiver who will also be informed of the study. Both members of the dyad will be allowed to discuss their participation in study and sign the consent forms.

Step 2 – After surgery, if patients experience delirium, their family caregiver will be phoned by the nurse-mentor to re-confirm their initial consent, and the dyad will be included in the study. For dyads randomized to the intervention to be eligible, the caregiver must agree to participate within 24 hours of delirium onset in order to ensure a prompt start to the intervention.

Informed consent is obtained from each participant in this study.

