#### Anticipated recruitment time

On average, 28 patients per week undergo CABG surgery or cardiac valve surgery with post-surgical recovery in the research hospital. A 40% incidence of delirium is estimated, which represents approximately 11 patients weekly. Our team’s past experience in the same research milieu with a study involving family caregivers in a highly similar context showed a recruitment rate of 30% [49]. Thus, a recruitment rate of one to two dyads weekly is expected and a total of 20 weeks is planned to reach a sample size of 30 dyads.

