The postoperative approach to recruitment implied specific ethical issues because patients with delirium lose their ability to give informed consent for the duration of their delirium. Given that the experimental intervention had little potential for deleterious effects, that a caregiver was involved, and that the patients would be able to consent after resolution of their delirium, the ethics committee allowed a new procedure for recruitment. This procedure included obtaining informed consent from the caregiver only during the delirium, followed by informed consent from the patient once the delirium resolved. The ethics committee’s decision was also based on a modified article of the Quebec Civil Code [52] which now allows the family to consent for the temporarily cognitively impaired parent in studies in which potential deleterious effects are minimal. This is parallel to the consent for care that can be provided by family members in clinical care settings when the ill person is unable to consent due to cognitive impairment. Therefore, in the present study, we obtain informed consent from caregivers when patients themselves are unable to consent. The patient has to consent for the study after emerging from the delirium before the time or outcome assessment at 1 month; the data collected in patients who cannot consent within that time frame are excluded from the study, as well as those for caregivers. This approach to recruiting patients is proving more effective than the initial approach.

In addition to this first challenge, our team experienced difficulty with delirium detection. In the research milieu, a delirium screening tool, the ICDSC, is administered three times a day as part of usual care for all post-surgical patients in the ICU, and as needed on the surgical ward. It was expected that delirious patients would be identified by a score of four or higher on the ICDSC, as recommended [19]. However, we observed that a number of patients with hypoactive delirium do not score four or more on the ICDSC. Hypoactive delirium is recognized by the scientific community as being highly underdiagnosed or misdiagnosed for depression because of its less behaviorally-disturbing nature [53, 54]. Until now, the most effective way to identify patients with hypoactive delirium has been to speak to all patients with a score of at least one on the ICDSC scale, and focus on identifying more subtle symptoms such as inattention or mild hallucinations.

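### The ±15.5% precision for the primary indicator uses the 30 dyads to be recruited as denominator, but the indicator is a share of caregivers approached (about 40 at 75% consent, ±13.4 points)

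*Protocol article*

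**What the plan says.** Table 4 of the protocol article, in the block on the study design, gives the primary indicator as "obtaining consent from at least 75% of the caregivers approached to participate in the study". The Outcomes text and the Discussion (Study limits) repeat it. Its denominator is therefore caregivers approached.

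The Sample size section says: "A convenience sample of 30 patient-caregiver dyads will be recruited". It takes "obtaining consent from a proportion of 75% of the caregivers approached to participate in the study" as the feasibility indicator and then states that "30 dyads is a sample large enough to estimate the proportion of caregivers that consent with a precision of ± 15.5" percent, "using a 95% confidence interval". Under Anticipated recruitment time, "a total of 20 weeks is planned to reach a sample size of 30 dyads". The 30 are thus the enrolment target.

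The article describes two ways of asking the caregiver:

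- **Original protocol (Recruitment).** The request came before surgery: "Both members of the dyad will be allowed to discuss their participation in study and sign the consent forms". If delirium followed, the caregiver was telephoned to re-confirm.
- **Amended procedure (Preliminary feasibility results).** The approach became postoperative: "This procedure included obtaining informed consent from the caregiver only during the delirium", with the patient's own consent sought once the delirium had resolved.

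The Outcomes section says that the recruitment variables are measured over the whole study. The article does not define which caregivers count as approached.

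**The concern.** A dyad can be recruited only if its caregiver has consented. Among 30 recruited dyads the caregiver consent rate is therefore 100% by construction, and 30 cannot be the denominator of a consent proportion expected to be 75%. The precision sentence puts the numerator of the indicator where its denominator belongs.

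This matters because 75% is the only numeric feasibility threshold in the article, and the precision statement is the only quantitative support for 30 dyads. If the same confusion reached the analysis, the reported interval would rest on the wrong count.

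A second question follows from the change in recruitment. With one undefined term for caregivers approached and two kinds of request during the study, a single proportion could mix answers to different questions.

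**Working it through.** **Inputs**

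- Assumed consent proportion p = 0.75 (Sample size).
- 30 dyads, described as recruited (Sample size; Anticipated recruitment time).
- Two-sided 95% interval, z = 1.96 (Sample size).
- Denominator of the indicator: caregivers approached (Table 4; Outcomes; Sample size).

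**Step 1. Reproduce the stated figure.** Wald half-width = z × √(p(1 − p)/n).

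With n = 30: 1.96 × √(0.75 × 0.25 / 30) = 1.96 × √0.00625 = 0.155, or ±15.5 points. Solving for n at a half-width of 0.155 gives 29.98. Other methods at n = 30 do not match: with continuity correction ±17.2 points; Wilson 57.3% to 87.0%; exact (Clopper-Pearson) 55.9% to 88.9%. The article used the plain Wald formula with 30 as denominator.

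**Step 2. Can 30 be the number approached?** 0.75 × 30 = 22.5, so 22 to 23 dyads would be recruited. That contradicts the target of 30.

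**Step 3. Use the indicator's own denominator.** Approached = 30 / 0.75 = 40.

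Wald: 1.96 × √(0.1875 / 40) = 0.134, or ±13.4 points. For 30/40 the exact interval is 58.8% to 87.3% and the Wilson interval is 59.8% to 85.8%.

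Difference from the stated figure: 15.5 − 13.4 = 2.1 points.

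**Step 4. Other consent rates, with 30 consents fixed.**

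| Consent rate | Approached (30/p) | Wald half-width (points) |
|---|---|---|
| 90% | about 33 | ±10.2 |
| 75% | 40 | ±13.4 |
| 60% | 50 | ±13.6 |
| 50% | 60 | ±12.7 |
| 30% | 100 | ±9.0 |

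With n = 30/p, the half-width becomes 1.96 × √(p²(1 − p)/30). It is largest at p = 2/3: 1.96 × √(0.1481/30) = 0.138. On the Wald scale it therefore never reaches 15.5 points at any consent rate.

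**Step 5. Limits of the calculation.** Recruiting to a fixed number of consents makes the number approached random, so any interval that treats it as fixed is an approximation. The exact interval is also asymmetric: at 30/40 its lower arm is 75.0 − 58.8 = 16.2 points and its upper arm is 87.3 − 75.0 = 12.3. Its total width, 28.5 points, is still below the 31.0 points implied by ±15.5.

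**The case against.** The strongest reply is that the slip harms nothing. On the Wald scale, precision is better than stated at every consent rate, so the claim that 30 dyads are enough for ±15.5 points survives. It is also only a planning figure, because the Statistical methods section already promises 95% intervals for the feasibility criteria from the observed data. This stands. It limits the point to a correction of a stated figure and does not challenge the sample size.

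A reader might infer that N = 30 now has no justification. The document does not support that. The Sample size section also relies on published literature on pilot studies and on the wish to show trends between the groups. The precision statement is the only quantitative ground, not the only one.

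A reader might also infer that the trial will pool preoperative and postoperative requests into one misleading rate. No text says so. Table 1 places caregiver screening and consent at delirium onset, which fits the amended procedure. Table 4 lists the effectiveness of recruitment strategies, and the Discussion promises a flowchart of approached participants. The full protocol or analysis plan, not shown here, may define the term. What remains is an inference: the route changed during recruitment, the indicator covers the whole study, and the article does not tie it to either route.

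Nor does the article show that most caregivers asked before surgery would never face delirium. The 40% incidence is for all patients, and no rate is given for the group with three or more risk factors to which preoperative screening was limited. It likewise does not say which recruitment route a larger trial would use.

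**Conclusion.** The denominator error is established from the text and the arithmetic. The ±15.5% arises only with n = 30, and 30 is the number recruited. On the indicator's own denominator the planning figure is about 40 approached and ±13.4 points, so the stated value is about 2 points too wide. This assumes 75% consent, recruitment to exactly 30 consenting dyads, and a binomial interval with the number approached treated as fixed. If dyads were excluded because the patient did not later consent and were then replaced, more than 40 caregivers would be approached and precision would improve slightly; the article does not say whether they are replaced.

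The error is conservative and leaves N = 30 intact. The point about the two recruitment routes is secondary and inferential: it supports a request for separate reporting, not a finding that the rate is biased.

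**What to change.** 1. **Sample size section.** Replace the precision sentence with one such as: *30 consenting dyads at 75% consent imply about 40 caregivers approached, giving a 95% confidence interval of about ±13.4 points (exact interval for 30/40: 58.8% to 87.3%).*
2. **Final analysis.** Compute the interval for the primary indicator on the number of caregivers approached, with an exact or Wilson method.
3. **Table 4 or the final report (secondary).** State who counts as approached. Give the consent proportion separately for caregivers first asked at delirium onset, for preoperative requests, and for re-confirmations of an earlier consent. Re-confirmers should not be combined with first-time requests: they had already agreed once, so adding them could raise the rate.

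The cost is about two sentences, with no change to sample size or conduct. Item 3 assumes that the records behind the promised flowchart show by which route each caregiver was asked; the article does not confirm this.

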#### Randomization

Given the setting of the research center’s ICU and post-ICU surgery wards, with one visitor room shared by both surgical units as the site of the nursing intervention, participant blinding to group assignment is not possible. This poses a risk of inter-group contamination. To reduce this risk, randomization of blocks of time will be used instead of individual randomization. Two-week blocks, followed by a washout period of one week will be assigned to either the control or intervention group. Thus, if a delirium episode is detected during a 2-week block allocated to control, this patient and their caregiver will be assigned to the control group and vice versa. Participants will not be informed of the present allocation of the 2-week block of time until after they have consented to the study. Delirium episodes detected during the 1-week wash out period will not be randomized or included in the study.

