### Data collection and analysis

#### Statistical methods

The planned analyses concerning all the primary objectives include descriptive statistics, which, along with 95% CI, will be used to portray the intervention and study design’s acceptability and feasibility criteria. Control and experimental group descriptions will be achieved using descriptive statistics reflected by n, mean, standard deviation, and median, minimum, and maximum for continuous variables and frequencies and percentages for categorical variables; 95% CIs will also be presented when appropriate. Finally, to evaluate the validity of cerebral _r_SO_2_, a Pearson or Spearman correlation will be used (depending on level of measurement) to correlate oximetry scores and scores obtained on the ICDSC, DI, and CAM-ICU at Days 1, 2, and 3 following the onset of delirium.

The planned analyses for the study’s secondary objective of preliminary efficacy will include the statistical methods detailed below. It should first be noted that this is a pilot study assessing the feasibility of a larger study and statistical analyses will be used to examine the preliminary effects of the intervention and determine any trend in the results as this study is not powered for statistical testing. For H1 relative to delirium severity, a repeated measure ANCOVA will be performed using the DI scores taken on Days 1, 2, and 3 following delirium onset. The initial scores on the ICDSC taken at delirium onset will be used as a covariate. Post-hoc tests will be performed if the omnibus test is significant for the group by time interaction. Such an interaction would imply that delirium severity is different between groups over the three days. Mixed models will be used so that a patient with missing data at Days 1, 2, and 3 following the onset of delirium will not be excluded from the analysis. The intent-to-treat principle will be respected; all the patients in the study will be included in the analysis according to their group of randomization. Because the pilot study will not be used to definitely assess the efficacy of the intervention (this would be the objective of the larger study), we plan to conduct a sensitivity analysis using the last observation carried forward.

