For hypothesis H2 on adverse clinical complications following onset of delirium, a combined outcome measure will be used (mention in the hospital chart of sternal wound dehiscence, a fall, respiratory tract infection, or accidental removal of urinary catheter, drain, arterial line or endotracheal tube = yes/no) and groups will be compared using a χ^2^ test.

Student’s T-tests for independent groups will be used for hypothesis involving continuous variables H3 on length of ICU and total hospital stay, H4 on psycho-functional recovery 1 month after the onset of delirium, H5 on caregiver’s anxiety level, and H6 relative to caregiver’s sense of self-efficacy. The planned treatment for missing data for hypotheses H3 to H6 is assigning the value corresponding to the group mean.

Assumptions underlying the planned models will be checked and alternative methods may be used if more appropriate. A significance level of 0.05 will be used for all analyses.

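### The sample-size section claims that 30 dyads will highlight any trend or possible difference between groups; no calculation supports this, and it conflicts with the plan's own statement on power and its 0.05 criterion (minor)

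*Protocol article*

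**What the plan says.** The Sample size section gives two grounds for N = 30. One is the pilot-study literature: "A convenience sample of 30 patient-caregiver dyads will be recruited based on the specific published literature on pilot studies". The other is precision for the main acceptability indicator, consent from 75% of the caregivers approached: "30 dyads is a sample large enough to estimate the proportion of caregivers that consent with a precision of ± 15.5% using a 95% confidence interval". It then adds a third benefit, without a calculation: "the chosen sample size will enable us to highlight any trend or possible differences in patient and caregiver outcomes between the two study groups".

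The Statistical methods section describes the efficacy analyses differently. They are meant to examine preliminary effects and "determine any trend in the results as this study is not powered for statistical testing". It also says that "the pilot study will not be used to definitely assess the efficacy of the intervention (this would be the objective of the larger study").

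The same section nevertheless plans a test for every hypothesis:
- **H1:** a repeated-measures ANCOVA/mixed model, with post-hoc tests only if the group-by-time interaction is significant.
- **H2:** a chi-square test.
- **H3 to H6:** t-tests ("Student’s T-tests for independent groups will be used for hypothesis involving continuous variables H3 on length of ICU and total hospital stay", and likewise for H4 to H6).

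It closes with one criterion: "A significance level of 0.05 will be used for all analyses".

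Confidence intervals are mentioned for the acceptability and feasibility criteria and, where appropriate, for the group descriptions. The article does not clearly plan them for the between-group differences.

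**The concern.** Three statements have to agree and do not: a claim that the sample will bring out any trend or possible difference, a disclaimer that the study is not powered for testing, and a 0.05 criterion applied to every analysis. The plan gives no other yardstick for H1 to H6, and it does not say what a trend is.

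The secondary objective, the preliminary effect of the intervention, is at stake. If the results for H1 to H6 are presented mainly as significant or not, most moderate true effects will appear as non-significant. The sentence in Sample size then invites a reader to think that a trend would have shown itself had there been one. Conversely, any t-test comparison that does cross 0.05 must show an observed difference of at least about 0.75 SD, which overstates any smaller true effect. The primary objective, acceptability and feasibility, is not touched.

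**Working it through.** **Inputs from the article.** N = 30 dyads in two groups; significance level 0.05; expected consent proportion 0.75; t-tests for H3 to H6; mixed model with a covariate for H1; chi-square for H2.

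**Assumptions, because the article does not give them.** 15 dyads per group (no ratio is stated, and allocation is by time block: "Two-week blocks, followed by a washout period of one week will be assigned to either the control or intervention group"); two-sided testing; independent observations; no missing data. Effects are in units of the between-person SD.

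**1. The plan's own figure.** 1.96 × √(0.75 × 0.25 / 30) = 0.155. The stated ±15.5% reproduces.

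**2. Precision for H3 to H6.** Half-width of the 95% CI for a mean difference = t(0.975, 28 df) × √(2/15) = 2.048 × 0.365 = 0.748, or about 0.75 SD. This is also the smallest observed difference that reaches p < 0.05.

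**3. Power for H3 to H6** (noncentral t, 28 df):

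| True difference (SD) | Power |
|---|---|
| 0.3 | 12.5% |
| 0.5 | 26% |
| 0.74 | 50% |
| 0.8 | 56% |
| 1.0 | 75% |
| 1.06 | 80% |

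**4. Sensitivity of the 80% power figure.**
- One-sided 0.05, normal approximation: (1.645 + 0.842) × √(2/15) = 0.91 SD. The two-sided normal approximation, for comparison, is (1.960 + 0.842) × 0.365 = 1.02 SD.
- Unequal arms: 18/12 gives 1.08 SD and 20/10 gives 1.12 SD.
- Correlation within time blocks: 20 planned weeks at 3 weeks per cycle is about 6.7 blocks of about 4.5 dyads. The design effect is 1 + 3.5 × ICC. With assumed ICCs of 0.01, 0.05 and 0.10 the detectable difference is 1.08, 1.15 and 1.23 SD.

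**5. H1.** For the mean of the three daily scores adjusted for a baseline covariate, the variance factor is (1 + 2ρ)/3 − r², with ρ the correlation between days and r the correlation of the covariate with the daily scores. Neither is given.
- ρ = 0.5, r = 0.5: factor 0.417, so 1.06 × √0.417 = 0.68 SD.
- ρ = 0.8, r = 0: factor 0.867, so 1.06 × √0.867 = 0.99 SD.

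The range is thus about 0.68 to 0.99 SD for the three-day mean. It does not describe the interaction test that gates the post-hoc comparisons.

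**6. H2.** No event rates are given, so these are illustrative. Exact power of the uncorrected chi-square test at 15 per group is 23% for 40% versus 20%, and 73% for 50% versus 10%. At 40% versus 20% the 95% CI half-width for the risk difference is 1.96 × √((0.4 × 0.6 + 0.2 × 0.8)/15) = 0.32, or ±32 percentage points.

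**7. Direction only.** The probability that the observed difference has the right sign is Φ(d/√(2/15)): 71% at 0.2 SD, 79% at 0.3 SD and 91% at 0.5 SD.

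**The case against.** The strongest reply is that the article already says what needs saying. It disclaims power for testing, leaves efficacy to a larger study, and in Preliminary feasibility results assigns adequate power to that study. N = 30 rests on pilot literature and on the consent proportion; the disputed sentence is an addition, and removing it changes nothing in the design. Low power for secondary outcomes is normal in a pilot. All of this stands, and it is why the point is minor.

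A second reply is that highlighting a trend is not the same as detection at p < 0.05. This also stands in part: the article does not define a trend by significance, and a 0.5 SD effect would point the right way about 91% of the time. But the sentence promises any trend and also possible differences, and at 0.2 to 0.3 SD the sign is wrong in about 21% to 29% of trials. The claim is too broad on either reading.

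A third reply is that intervals for between-group differences are a reporting detail that a condensed article may leave to its analysis plan. That is fair for their absence alone. It does not cover the 0.05 criterion and the significance gate for H1, which the article does fix.

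Some stronger inferences are tempting and are not supported:
- **That the sample size is wrong.** Its stated precision for consent reproduces.
- **That the investigators will read non-significance as no effect, or will size or launch the larger trial on the observed effect.** The article commits to neither.
- **That nothing under one SD can be detected.** The figure of about one SD is for 80% power in the H3 to H6 t-tests. An effect of 0.8 SD would be significant 56% of the time, and H1 may be more sensitive.
- **That the assumptions used here all favour the plan.** Two-sided testing does not. The hypotheses are directional and the article does not state sidedness.

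**Conclusion.** The point holds as a minor inconsistency. The Sample size section claims a property that the design does not have, the Statistical methods section disclaims it, and the 0.05 criterion with the H1 gate sits badly with that disclaimer.

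For H3 to H6 the sample gives an interval of about ±0.75 SD and 80% power at about 1.06 SD; true effects below about 0.74 SD would be non-significant more often than not. These figures assume 15 per group, two-sided testing, independent dyads and complete data. One-sided testing lowers the 80% figure to about 0.9 SD; unequal arms or correlation within time blocks raise it. For H1 the corresponding range is about 0.68 to 0.99 SD under assumed correlations, and for H2 no figure can be fixed without event rates. No increase in N is called for.

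**What to change.** 1. **Sample size.** Replace the disputed sentence with what N = 30 delivers, in line with the Statistical methods section. For example: *With about 15 dyads per group, the 95% CI for a between-group difference in a continuous outcome will be about ±0.75 SD; the sample is not intended to detect or exclude differences in outcomes.* Keep the consent-based justification as it is.
2. **Statistical methods, H1 to H6.** Report estimated between-group differences (a risk difference for H2) with 95% CIs, and do not judge them against 0.05.
3. **Statistical methods, H1.** Report the day-specific group differences with their intervals whether or not the interaction is significant.

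This needs no new data, dyads or assessments. The cost is a few lines of text and a less favourable stated claim for N = 30.
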